## Abstract

**Introduction:**

Colon cancer remains one of the most prevalent cancers worldwide. Unfortunately, there are no recognized and effective therapeutic strategies to prevent tumor recurrence after radical resection and chemotherapy, and the disease-free survival (DFS) in patients with stage IIIB or IIIC disease remains unsatisfactory. Xian-Lian-Jie-Du optimization decoction (XLJDOD) is a Chinese herbal medicine (CHM) empirical prescription, which has been validated experimentally and clinically that could inhibit the progression of colorectal cancer and ameliorate the symptoms. The purpose of this study is to evaluate the efficacy and safety of XLJDOD in prevention of recurrence of colon cancer.

**Methods:**

This study is a multi-center, double-blind, randomized, placebo-controlled trial conducted at 13 hospitals of China. Following the completion of surgery and adjuvant 5- fluorouracil-based chemotherapy, a total of 730 subjects with stage IIIB or IIIC colon cancer will be randomized in a 1:1 ratio to an intervention group (*n* = 365; XLJDOD compound granule) and a control group (*n* = 365; Placebo). Patients will receive 6-month treatments and be followed up with 3 monthly assessments for 2 years. The primary outcome is 2-year DFS rate and the secondary outcomes are 1, 2-year relapse rate (RR), overall survival (OS) and quality of life (QoL). Safety outcomes such as adverse events will be also assessed. A small number of subgroup analysis will be carried out to explore the heterogeneity of effects of XLJDOD.

**Discussion:**

The outcomes from this randomized controlled trial will provide objective evidences to evaluate XLJDOD’s role as an adjuvant treatment in colon cancer.

**Trial registration:**

www.ClinicalTrials.gov, identifier: NCT05709249. Registered on 31 Jan 2023.

**Supplementary Information:**

The online version contains supplementary material available at 10.1186/s12906-023-04052-2.

## Introduction

According to estimates from the International Agency for Research on Cancer (IARC), colorectal cancer has the third highest incidence and the second highest mortality worldwide in 2020, in which the occurrence and death risk of colon cancer is about half higher than that of rectal cancer. The prevention and control situation is still grim with about 1.15 million new cases and about 0.58 million deaths due to colon cancer in 2020 [1]. For those without evidence of metastatic disease, surgical resection is the main treatment modality, and it is commonly followed by adjuvant chemotherapy, which can bring survival benefits for patients with colon cancer [2, 3]. Unfortunately, approximately 1/3 of patients have stage III disease at diagnosis because of lymph node involvement [4–6], around 40% of them relapse even after surgery and adjuvant chemotherapy [7, 8].

The main cause of death after radical resection for colon cancer is tumor recurrence [9]. The study found that the risk of recurrence is highest in the first 2 years and that the risk of death peaks about 2 years after treatment [10]. Stage III colon cancer comprises a highly heterogeneous group of patients, with a 2-year rate of disease-free survival (DFS) of about 91% (IIIA), 79% (IIIB) and 60% (IIIC), respectively [11]. In addition, high levels of symptom burden-fatigue, insomnia, distress, constipation, and diarrhoea-is often expected shortly after treatment, which can result in significant limitations in daily activities and overall impairment in health-related quality of life (QoL) [12]. However, there lacks a recognized and effective therapeutic strategy in modern medicine to prevent recurrence after radical resection and chemotherapy for patients with stage IIIB or IIIC colon cancer. Additional strategies are required urgently in consequence.

Traditional Chinese medicine (TCM) is an important part of comprehensive treatment of cancer, which has been proven to prevent recurrence of many tumors [13–15]. In the past few years, traditional Chinese herbal medicine (CHM) has gained more and more attention in the field of colorectal cancer due to its favorable safety and efficacy profiles. A great quantity of Chinese patients with colon cancer seek help from TCM during or after standard first-line therapy. Prospective cohort studies confirmed that long duration of TCM herbal use was associated with improved disease-free survival outcomes in patients with stage II and III colorectal cancer [16–18]. A retrospective cohort study indicated that adherence to medication of TCM after surgery could significantly improve disease-free survival in colorectal patients with stage III disease [19]. Furthermore, a randomized controlled trial of 370 patients showed that Chinese herbal formula composed of seven herbs (PRM1201) in combination with adjuvant chemotherapy in the treatment of stage III colon cancer could effectively increase the 3-year DFS rate and improve their life quality [20].

On the basis of inheriting the theory of cancer toxin [21], Xian-Lian-Jie-Du optimization decoction (XLJDOD, original name: Xian-Lian-Jie-Du decoction) was developed by [name] to inhibit the progression of colorectal cancer. The herbal drugs of XLJDOD is shown in Table 1. A preliminary randomized controlled clinical study with 60 subjects revealed that XLJDOD combined with capecitabine plus oxaliplatin (CAPOX) could promote cellular immune function of patients with advanced colorectal cancer, enhance their QoL and tolerance to chemotherapy [22].

**Table 1 Tab1:** Standard formulation of Xian-Lian-Jie-Du Optimization Decoction (XLJDOD)

Pinyin name	Latin name	Pharmacological effects	Doses, g
Huangqi	*Astragali Radix*	regulate immune function, affect cell cycle, promote apoptosis and neovascularization, inhibit inflammation response and reverse multi-drug resistance [23]	30
Baizhu	*Atractylodis Macrocephalae Rhizoma*	induct tumor cell apoptosis, inhibit tumor stem cell characteristics, regulate metabolic activity, inhibit invasion and metastasis, reverse chemoresistance, overcome tumor immune evasion [24]	12
Sanleng	*Sparganii Rhizoma*	one of the most frequently used herb pairs: inhibit cell proliferation, migration, invasion and stemnes, cycle arrest, regulate immunity, anti-angiogenesis [25, 26]	9
Ezhu	*Curcumae Rhizoma*		9
Yiyiren	*Coicis Semen*	promote apoptosis, reduce expression of tumor related genes, suppress chronic inflammatory microenvironment, enhance immune function [27]	15
Huanglian	*Coptidis Rhizoma*	induct apoptosis, anti-inflammation, modulate gut microbiota, regulate signal transduction, inhibit metastasis, inhibit autophagy [28]	3
Kushen	*Sophorae Flavescentis Radix*	induce cell cycle arrest, inhibit angiogenesis, induce cell differentiation, inhibit tumor metastasis and invasion, reverse multidrug resistance [29]	6
Xianhecao	*Agrimoniae Herba*	promote apoptosis and necrosis, block cell cycle, inhibit migration and invasion,enhance immune response [30]	12

However, a high-quality randomized controlled trial with sufficient sample sizes is still required urgently to prove the long-term efficacy and safety of XLJDOD in individuals with colon cancer, especially those with stage IIIB or IIIC disease who are at high risk of recurrence. Therefore, we designed such a randomized controlled trial aimed at evaluating the utility of XLJDOD as an adjuvant treatment in preventing postoperative recurrence, prolonging survival and improving QoL of people with stage IIIB or IIIC colon cancer. The purpose of this study is to present the methodologies and details of the protocol.

## Methods and design

### Study design

This study is designed as a multicentre, randomized, double-blind, parallel-arm, placebo-controlled trial. Participants will be recruited from following 13 centers, including Sun Yat-sen University Cancer Center, Cancer Hospital Chinese Academy of Medical Sciences, Fudan University Shanghai Cancer Center, West China Hospital of Sichuan University, Jiangsu Province Hospital, Zhejiang Cancer Hospital, Jiangsu Province Hospital of Chinese Medicine, LongHua Hospital Shanghai University of Traditional Chinese Medicine, The First Affiliated Hospital of Guangzhou University of Chinese Medicine, Jiangsu Province Hospital on Integration of Chinese and Western Medicine, The First Affiliated Hospital of Guizhou University of Traditional Chinese Medicine, The First Affiliated Hospital of Soochow University, and The First People’s Hospital of Changzhou. Recruitment performs simultaneously in out-patient clinics and wards. This trial was registered with ClinicalTrials.gov (NCT05709249). This protocol has been developed in accordance with the Standard Protocol Items: Recommendations for Interventional Trials (SPIRIT) [31], and the new extension of the Consolidated Standards of Reporting Trials (CONSORT) for CHM [32] to ensure appropriate high-quality methodology and strict quality control. The clinical study will be conducted for 36 months, from December, 2022 to December, 2025. The flow diagram of this study is depicted in Fig. 1.

**Fig. 1 Fig1:**
[figure not shown]
The flow diagram of this study

### Inclusion criteria

1. Colon carcinoma entirely lying above the peritoneal reflection confirmed by pathology.2. Completion of surgical resection of tumors with negative margins (R0 resection) and at least 3 months of adjuvant chemotherapy based on 5-fluorouracil (5-FU). **4 cycles of CAPOX (capecitabine and oxaliplatin), 6 cycles of FOLFOX (fluorouracil, leucovorin, and oxaliplatin) or 4 cycles of single agent-5-FU, etc.3. Within 3 months after the completion of adjuvant chemotherapy.4. Patients with Stage IIIB or IIIC disease.**IIIB: T3-T4aN1/N1cM0, T2-T3N2aM0 and T1-T2N2bM0, IIIC: T4aN2aM0, T3-T4aN2bM0 and T4bN1-N2M0, as defined by the American Joint Committee on Cancer (AJCC) 8th edition) [6].5. Aged 18–80 years, men or women.6. Eastern Cooperative Oncology Group (ECOG) performance status of 0–2.7. With no radiographic evidence of tumor recurrence.8. Sign the informed consent form.

### Exclusion criteria

1. Presence of other malignancies in the past 5 years except curatively treated basal cell carcinoma or cervical carcinoma in situ.2. Besides adjuvant chemotherapy, other adjuvant therapy such as radiotherapy, targeted therapy and immunotherapy has been used to treat colon cancer.3. Antitumor Chinese patent medicine and decoction have been used for more than 3 months after surgery or within 1 month before enrollment.4. Patients with severe comorbidities such as cardiovascular, cerebrovascular, renal, hepatic, hematopoietic system and other severe primary diseases.5. Allergic to the ingredients of XLJDOD.6. Any condition that is unstable or can jeopardize the safety of the patients and their compliance to the study, including pregnancy, plan to be pregnant, lactation and psychiatric disorders (schizophrenia, depression, and obsessive-compulsive disorder, etc.).7. Suspected or confirmed history of alcohol and drug abuse.8. Patients with other conditions considered by the investigator should not participate in the study.9. Patients who have recently participated in or are currently participating in other clinical trials of drugs.

### Withdrawal criteria

The investigator can decide to withdraw a subject from this study in the following circumstances:1. Patients with anaphylaxis or serious adverse events (SAEs) who require the discontinuation of treatment.2. Patients failure to comply with medication protocol (e.g., taking less than 80% or more than 120% of the prescribed dosage, adding other treatment drugs without following the investigator’s guidance).3. Patients who break blind procedure for a variety of reasons.

The patients can discontinue their participation in the study at any time for any reason without any consequences if they are unwilling or impossible to proceed. Lost to follow-up patients who are not explicitly asked to withdraw from the trial but no longer receive experimental drug or undergo testing are also considered as withdrawn.

### Intervention measures

#### Intervention group

Subjects in the intervention group will be treated with XLJDOD compound granule. Treatment will begin within 3 months after standard adjuvant chemotherapy and compliance will be continuously monitored. XLJDOD will be taken twice a day, infused with warm water, 1 h after lunch and dinner. One course of treatment will take 28 days in 1 month, and 2- to 3-day rest. Treatment will continue for 6 courses.

#### Control group

Subjects in the intervention group will be treated with placebo (XLJDOD mimetic agent). Placebo granules contains 2% XLJDOD granules, and the remaining ingredients are 86.13% maltodextrin, 10% lactose, 1.28% caramel pigment, 0.08% lemon yellow pigment, 0.01% sunset yellow pigment, and 0.50% bitters. The course of placebo in control group will be in accordance with that of XLJDOD in intervention group. After the treatment, the packaging will be returned to the investigators.

#### Drug combination

All drug treatment received by subjects during the trial including the baseline should be recorded in detail in the case report form (CRF). Necessary treatment under the guidance of the clinician due to other diseases or symptoms is allowed, however, Chinese patent medicine and decoction with antitumor effects should be prohibited before the termination of the trial.

### Study procedure

The duration of this study will be 3 years, with 1 year of enrollment and a minimum follow-up period of 2 years. The specific measurements and time points for data collection of this study are outlined in Fig. 2, which must be followed as accurately as possible. Treatment will be started within 7 days of the randomization and last for 6 months. Eligible patients will be followed up every 3 months until death or the end of this study. The researcher should obtain written informed consent before conducting study-specific procedures for patients enrolled in the trial.

**Fig. 2 Fig2:**
[figure not shown]
Clinical Study Schedule Form. 1 Including chest, abdomen, and pelvis computed tomography (CT) or enhanced CT scan, patients with conditions can undergo pelvis magnetic resonance imaging (MRI) scan; At baseline, patients can provide imaging reports within 3 months. 2 Colonoscopy report within 3 months is only required for patients without preoperative colonoscopy due to obstructing lesion. 3 Safety data will be reviewed every 3 months during treatment, and reviewed in accordance with the guidelines and clinician recommendations after medication intervention. 4 Plasma will be collected before and after medication and placed in –80 °C refrigerator

### Outcomes

#### Primary outcome

Two-year disease-free survival (DFS) rate: DFS is defined as the time from the date of randomization to the date of disease recurrence, second primary cancer (colon cancer or other cancer), or death from any cause, whichever occurred first. 2-year DFS rate is defined as the percentage of patients alive without disease recurrence at 2 years measured from the randomization date. Disease recurrence includes any condition of the following—unequivocal radiological evidence of colon cancer locoregional recurrence or distant metastases, positive histology or cytology (e.g. peritoneal or pleural cytology), colonoscopic evidence of locoregional cancer recurrence at the anastomotic site and its adjacent areas.

#### Secondary outcomes

One, two-year relapse rate (RR): RR is defined as the fraction of followed patients who have disease recurrence. All disease recurrences and deaths from colon cancer are events. Second primary same cancers and other primary cancers will be ignored.

Overall survival (OS): OS is measured from the date of enrollment to the date of death, irrespective of cause.

Quality of life (QoL):

1. Changes in total score on the EORTCQLQ-C30 Scale: The changes of EORTCQLQ-C30 score will be compared in the two groups prior to and following XLJDOD compound granule administration. Considering that some items of EORTC QLQ-CR29 scale are targeted at colostomy patients with rectal cancer, we select the EORTCQLQ-C30 Scale. It is a universal scale for all patients with malignant tumors with a total score of 126, ranging from 30 (least severe) to 126 (most severe). Measurement will be performed at baseline and month 6, 12 ,18 ,24.

2. Changes in total score on the MD Anderson Symptom Inventory for Traditional Chinese Medicine (MDASI-TCM): Compared with the baseline period, the changes in MDASI-TCM score at month 6, 12 ,18 ,24 will be measured. The scale is divided into two parts. The first part mainly assesses the severity of 20 common clinical symptoms and TCM-related symptoms of patients with cancer in the past 24 hours. The second part is the evaluation scale of the interference of the above symptoms with daily functioning [33]. It has a total of 26 items, each with a score of 0–10, leading to a total score of 0–260.

#### Safety outcomes

1. Prevalence of abnormal vital signs (pulse, respiration, blood pressure and body temperature). Measurement will be performed at baseline and every 3 months within 2 years of follow-up.2. Prevalence of abnormal blood routine, urine routine, stool routine, liver and kidney function tests. Measurement will be performed at baseline and every 3 months during treatment, and performed in accordance with the guidelines and clinician recommendations after medication intervention.3. Other adverse events (AEs) and serious adverse events (SAEs). All adverse events should be recorded and graded in Adverse Event Form throughout the study. At the same time, the relationship between the adverse event and XLJDOD compound granule should be evaluated, and the treatment process and outcome should be recorded in detail until the laboratory examination returns to normal and the symptoms and signs disappear. When a severe adverse event occurs, immediate measures should be taken to protect the safety of the patients. Researchers must complete the Serious Adverse Event Report Form and report to the research center, the main research medical ethics committee, and the primary sponsor within 24 hours.

#### Exploratory outcomes

Plasma samples will be collected before and after medication and will be used to establish a biological sample bank, which may help to promote the research program and explore the therapeutic mechanism of XLJDOD in preventing colon cancer recurrence. At the same time, tongue images (the colour, size and shape of the tongue and the colour, thickness and moisture content of the tongue coating) will be extracted by the Chinese medicine artificial intelligence health status recognition system to investigate the value of tongue images in the prediction of colon cancer recurrence.

### Randomization and allocation concealment

In this trial, an online centralized randomization system called Interactive Web Response System (IWRS) will perform the block randomization with a 1:1 ratio, permutation block with variable sizes of four, six, eight, or twelve, stratified by the study center. After informed consent, the investigators will log into IWRS to acquire a unique identification code and random number of each participant for participant identification and treatment assignment. IWRS will ensure the allocation concealment. It will only offer a random number to the investigator, and none of the investigators, participants, and outcome evaluators will know from random numbers whether they represent the intervention group or the control group. In case of SAEs that may be associated with experimental drugs, including death, allergic reactions, intolerable severe gastrointestinal reactions, liver and kidney insufficiency, etc., the allocated intervention of participant could be revealed by investigator in the IWRS.

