### Blinding

A double-blind design was adopted in this study. Investigational drugs are XLJDOD compound granule and XLJDOD mimetic agent, which are produced, packaged and provided by Tianjiang Pharmaceutical Group Co. Ltd., Wuxi, China. Mimetic agent is indistinguishable from XLJDOD compound granule in shape, size, taste, color, package, and Lot number. Each medication bag will be labelled with a unique identity number, which corresponds to the random number obtained by IWRS. Researchers, participants, statisticians, and data administrators will be blind to the treatment allocation plans throughout the trial in order to reduce the bias to the greatest extent.

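### Possibly drug-related death is a stated ground for the investigator to open the code, which exposes causality and cause-of-death judgements and cannot help the patient

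*Protocol article*

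**What the plan says.** Under Randomization and allocation concealment, the protocol article gives the grounds for unblinding one participant: "In case of SAEs that may be associated with experimental drugs, including death, allergic reactions, intolerable severe gastrointestinal reactions, liver and kidney insufficiency, etc". In that event "the allocated intervention of participant could be revealed by investigator in the IWRS". Suspected relation to the trial drug is a condition. Need for the allocation is not, and the list is left open.

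The Blinding section states the general rule without an exception: "Researchers, participants, statisticians, and data administrators will be blind to the treatment allocation plans throughout the trial".

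Three outcome definitions bear on this:

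- Safety outcomes: for adverse events, "the relationship between the adverse event and XLJDOD compound granule should be evaluated".
- Secondary outcomes, relapse rate: "All disease recurrences and deaths from colon cancer are events". Other deaths are therefore not relapse events.
- Primary outcome and overall survival: DFS ends at recurrence, "second primary cancer (colon cancer or other cancer), or death from any cause, whichever occurred first", and "OS is measured from the date of enrollment to the date of death, irrespective of cause".

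The Withdrawal criteria also allow the investigator to withdraw "Patients who break blind procedure for a variety of reasons".

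**The concern.** The usual reason to give a site the code is that someone treating the patient needs it. The rule here turns on the kind of event instead, and it names death first. After a death no decision about that patient remains, so unblinding the site gains nothing for the patient. If a regulator or ethics committee needs the allocation, it can be released without the site seeing it.

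What is lost is protection for two matters of judgement. One is the relationship of the event to XLJDOD. The other is the cause of death, which decides whether a death without earlier recurrence enters the 1- and 2-year relapse rate. The article does not place either judgement before the code is opened.

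The listed non-fatal events raise a related issue. A survivor remains on 3-monthly follow-up, and recurrence is part of the primary outcome. If the code was opened without need, the site follows that patient unblinded for no benefit.

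**Working it through.** No planned figure is at issue, so the check sets the sections side by side.

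1. **Who and when.** The investigator may open the code in the IWRS if an SAE may be drug-related. A first suspicion of drug relation therefore exists before the code is opened. The final causality and cause-of-death entries are not stated to precede it.

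2. **What a death contributes to each outcome.**

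| Outcome | Deaths counted | Can attribution change it? |
|---|---|---|
| DFS (primary) | any cause | no |
| OS | any cause | no |
| Relapse rate | colon cancer only | yes, if no recurrence was recorded before |
| Safety causality | each adverse event assessed | yes |

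3. **How often the relapse-rate route can matter.** A death must be suspected of drug relation, have no recurrence already recorded, and have a cause open to dispute. Patients enter after R0 resection without radiographic recurrence and are seen every 3 months. Most colon cancer deaths should therefore follow a recurrence that has already been counted. This is reasoning from the design, not a figure in the document.

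4. **Survivors.** Attribution plays no part here; the route is knowledge of the allocation during later follow-up. The primary outcome requires unequivocal imaging, positive histology or cytology, or colonoscopic evidence, which limits how far that knowledge can move a recurrence call. It does not remove the influence entirely.

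5. **Can the size be computed?** The planning rates give 365 × 0.30 + 365 × 0.20 = 109.5 + 73 = 182.5 DFS events by 2 years, if all 730 patients are followed. Every death by 2 years falls in a patient with a DFS event, so this is only an outer limit on deaths under those assumptions. The document gives no rate for deaths, for deaths suspected of drug relation, or for code-breaks. The number of exposed judgements cannot be derived.

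6. **The two blinding statements.** The Blinding section promises blinding throughout; the section before it permits individual unblinding. Read together they are a rule and an exception, but the rule does not mention the exception.

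**The case against.** The strongest reply is that this is an ordinary safety provision in a condensed article. It applies only to events that may be drug-related, it is permissive, and the detail of who receives a code and which form comes first belongs in the full protocol. Adverse events are to be assessed for drug relation as they are recorded, and serious ones reported within 24 hours, so causality may well be entered blind. The randomization section also names outcome evaluators separately from investigators, so the person who opens a code need not be the one who judges recurrence. The Statistical analysis section compares rates of abnormal subjects between groups and does not mention attributed events.

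Most of this stands, and it limits the point. It does not answer the part the article states outright: death is a ground for site-level code-break, and need is not a condition.

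A reader might infer more. These stronger readings are not supported:

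- **Any death opens the code.** The text requires possible relation to the trial drug.
- **The primary result is biased through attribution of deaths.** DFS and OS count all deaths.
- **Once placebo is known, the event must be called unrelated.** The placebo contains 2% XLJDOD, plus lactose and pigments, so a relation is not excluded, although knowing the allocation would push the judgement.
- **Unblinding will fall unequally on the arms.** This is plausible for the listed reactions, but no data in the document show it.
- **The Blinding section flatly contradicts the code-break rule.** A missing cross-reference is the fairer description.

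**Conclusion.** The point holds in a limited form. The code-break rule is tied to event type and includes death, where unblinding the site cannot benefit the patient and leaves avoidable room for unblinded judgement. The exposure is confined to the relapse rate (through cause of death), the causality assessment of serious events, and the follow-up of what are likely to be few unblinded survivors. Its size cannot be computed, and it is probably small.

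The conclusion assumes that the full protocol does not already require causality and cause of death to be recorded before release. If it does, only the listing of death, the missing need condition and the missing cross-reference remain. If the withdrawal criterion on broken blinds is read to include code-breaks, a needless code-break could also lead to a patient being withdrawn; the text leaves this unclear. This is an inexpensive improvement and does not threaten the primary analysis.

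**What to change.** - Remove death from the grounds on which the site may open the code, and make site-level release conditional on the allocation being needed for the patient.
- For deaths and other non-emergency requests, have the relationship to XLJDOD and, where relevant, the cause of death recorded before any release.
- Where a regulator or ethics committee needs the allocation, release it outside the site.
- Do not put a form lock before an emergency code-break.
- State in the Blinding section that the code-break rule is the exception to blinding throughout the trial.

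The cost is a short protocol amendment and an IWRS/eCRF setting. Recruitment was still under way when the article was submitted, so the change can apply to later events. The downside is one more form step for non-emergency requests.
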